### 5.5 Dose Delays

#### 5.5.1 Dose Delays Due to Toxicity

- Dose delays for vaccines and CDX-1127

In circumstances where assessment of an AE is limited, such as by intercurrent illness, or when laboratory studies are required to assess for other causes of toxicity, the vaccine\* and/or CDX-1127 schedule may be interrupted for up to 21 days.

- If a toxicity can be clearly attributed to either the vaccine or CDX-1127, then only the investigational drug that caused the toxicity will be delayed.
- One vaccine and/or one CDX-1127 delay up to 21 days is allowed if due to an AE, regardless of attribution.
- If there is more than one vaccine and/or one CDX-1127 delay by 7 days or more due to an AE, regardless of attribution, the investigational drug that caused the toxicity should be discontinued. The remaining investigational drug may be continued.
- Missed doses may be shifted. Participants who are treated outside of the established schedule should return to the original schedule as soon as possible, keeping in mind that there must be at least a minimum of 6 days in between CDX-1127 infusions and a minimum of 5 days in between vaccines.

\*The vaccine includes all components that make up the vaccine (e.g.6MHP + Montanide ISA-51 with or without).

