#### 5.5.2 Delayed Visits for Reasons Other Than Toxicity

A schedule for return visits should be established at the first visit. If a participant misses a treatment, the missed treatment will be administered as soon as possible, so that subsequent treatments will be given in the appropriate intervals. Treatment may be continued for an additional time period, if needed. Participants who are treated outside of the established schedule should return to the original schedule as soon as possible keeping in mind that there must be at least a minimum of 6 days in between CDX-1127 infusions and a minimum of 5 days in between vaccines.

Note: Labs and study treatment/procedures may occur on different days as long as each occurs within the specified established window.

Table 7 defines what constitutes a delayed visit, whether the participant should continue to be treated, and whether a protocol violation should be reported and recorded. The range of days is counted from the original scheduled date.

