| Vaccine 3                                     |                                  |                                                                                                       |                           |
| Day 15                                               | ± 2 days                         | Vaccine/Labs                                                                                          | No                        |
|                                                      | ± 3 to 7 days                    | Vaccine/Labs                                                                                          | Yes                       |
|                                                      | ± 8 or more days                 | Labs                                                                                                  | Yes                       |
| Assessment/Biopsy                             |                                  |                                                                                                       |                           |
| Day 22                                               | ± 2 days                         | Biopsy/Labs                                                                                           | No                        |
|                                                      | ± 3 to 7 days                    | Biopsy/Labs                                                                                           | Yes                       |
|                                                      | ± 8 or more days                 | Labs                                                                                                  | Yes                       |
| Vaccine 4/Varlic                   |                                  |                                                                                                       |                           |
| Day 36                                               | ± 7 days                         | Vaccine/Varli/Labs                                                                                    | No                        |
|                                                      | ± 8 to 14 days                   | Vaccine/Varli/Labs                                                                                    | Yes                       |

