|                                                                                                                                                                                                                                                                                                                                                                                                                                                                                              | ± 7 days                      | Phone call                                                                                           | No                 |
|                                                                                                                                                                                                                                                                                                                                                                                                                                                                                              | ± 8 to 30 days                | Phone call                                                                                           | Yes                |
| a A participant will be taken off protocol treatment if more than one vaccination is delayed [3 days or more] during the treatment period.
b Scans are required for participants who complete the vaccine sequence and who are scheduled to complete day 183.
c Arm A only.
d If the day 176 visit is delayed, the day 183 visit needs to be 7 days later than the day 176 visit. This range of days applies around the 7 day interval. |                               |                                                                                                      |                    |

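### Table 7 footnote a contradicts the table it annotates: two vaccinations given inside deviation-free windows, or one treated 5-to-7-day delay at vaccine 2, meet its removal rule

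*Combined protocol and SAP*

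**What the plan says.** Section 5.5.2 says that Table 7 settles three things: what counts as a delayed visit, "whether the participant should continue to be treated", and whether a deviation is recorded. It adds: "The range of days is counted from the original scheduled date".

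For late vaccinations (other than for toxicity), the current schedule has these rows:

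- **Days 1, 8 and 15.** Up to 2 days: vaccine given, no deviation. 3 to 7 days: vaccine given, deviation recorded. 8 days or more: no vaccine.
- **Day 36.** Up to 7 days: "Vaccine/Varli/Labs", no deviation. 8 to 14 days: the same treatment, deviation recorded.
- **Day 176 (booster).** Up to 7 days: vaccine given, no deviation. 8 to 30 days: vaccine given, deviation recorded.

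Footnote a, attached to the range-of-days column, adds a cumulative rule: "A participant will be taken off protocol treatment if more than one vaccination is delayed [3 days or more] during the treatment period".

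Section 5.5.2 also requires "a minimum of 5 days in between vaccines" and says that participants treated off schedule "should return to the original schedule as soon as possible". Section 5.6 lists the reasons for stopping treatment. Footnote a's rule is not among them, unless it falls under noncompliance or investigator discretion.

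**The concern.** A cumulative cap can sit alongside per-visit windows. It cannot do so when visits that the table treats as on schedule are enough to reach the cap. A site following the rows would keep treating a participant whom the footnote removes, and a site following the footnote would remove a participant with no recorded deviation. Different sites may resolve this differently.

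What is at stake depends on when removal happens. Section 5.6 sends participants who stop treatment to the follow-up schedule in Section 9.1, where research bloods are drawn only at EOT 1 and EOT 2. Section 7.1.2 makes a participant evaluable for the primary immune endpoint through baseline plus day 127 assessments, progression before day 127, or stopping for a DLT. Removal for late visits before day 127 is none of these, so such a participant drops out of the persistent-response analysis unless progression also occurs before day 127. Section 5.7 appears not to allow replacement of someone already vaccinated. Removal at the booster comes after day 127 and instead puts the day 183 memory response at risk.

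**Working it through.** The plan states no figure on this point, so there is none to reproduce. The check sets the rules side by side.

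**1. Deviation-free visits against footnote a**

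| Vaccination | Given on | Days late | Deviation under Table 7 | Counts under footnote a (3 or more) |
|---|---|---|---|---|
| Vaccine 4 (day 36) | day 40 | 4 | No | Yes |
| Booster (day 176) | day 180 | 4 | No | Yes |

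That is two counted delays, so the removal rule is met with no deviation recorded. Any pair of delays of 3 to 7 days at these two visits does the same. Day 176 belongs to the treatment period: Table 7 lists it under that column heading, and the Section 9.1 calendars place it under active treatment.

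**2. Knock-on from vaccine 2 to vaccine 3**

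Inputs: planned days 8 and 15 (Section 5.2.1), minimum gap 5 days, and delay counted from the original date (both Section 5.5.2). If vaccine 2 is given on day 8 + d, the earliest vaccine 3 is day 8 + d + 5 = 13 + d. Its forced delay is (13 + d) − 15 = d − 2, or zero if that is negative.

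| Vaccine 2 delay d | Earliest vaccine 3 | Forced delay at vaccine 3 | Footnote a met by this alone |
|---|---|---|---|
| 2 | day 15 | 0 | No |
| 3 | day 16 | 1 | No |
| 4 | day 17 | 2 | No |
| 5 | day 18 | 3 | Yes |
| 6 | day 19 | 4 | Yes |
| 7 | day 20 | 5 | Yes |

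The same arithmetic links vaccine 1 to vaccine 2. It does not carry on to vaccine 4: vaccine 3 at 7 days late is day 22, so the earliest vaccine 4 is day 27, well before day 36. If the gap means five clear days (6 days from one vaccine to the next), the forced delay is d − 1 and the affected range is 4 to 7 days.

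**3. Illustration of size before day 127**

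The documents give no delay rates. Assume that each of the vaccines on days 8, 15 and 36 is independently 3 or more days late with probability q. Then P(2 or more of 3) = 3q²(1 − q) + q³.

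- q = 10%: 0.027 + 0.001 = 2.8%; 34 × 0.028 ≈ 1 participant
- q = 20%: 0.096 + 0.008 = 10.4%; 34 × 0.104 ≈ 4 (3.5)
- q = 30%: 0.189 + 0.027 = 21.6%; 34 × 0.216 ≈ 7

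The planned allowance is 34 − 30 = 4 (Section 7.2).

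**The case against.** The best defence is that the rows govern one visit and the footnote caps the total. On days 1, 8 and 15 that is a fair reading: a 3-to-7-day delay there is already a deviation, and treating after the first while stopping after the second is coherent. Section 5.6 also lists noncompliance as a ground for stopping. This narrows the clean contradiction to the deviation-free windows, now days 36 and 176 (also days 57 and 78 before v12-03-2020). It does not remove it, because a visit inside a deviation-free window is hard to call noncompliant.

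Several stronger readings are tempting but not supported:

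- **Any treated vaccine 2 delay forces a second one.** It does not. At 3 or 4 days, vaccine 3 still fits its 2-day window. Section 5.5.2 does say that "the missed treatment will be administered as soon as possible, so that subsequent treatments will be given in the appropriate intervals", and keeping the planned 7-day interval would extend the effect to all delays of 3 to 7 days. That sits badly with the 5-day minimum and the instruction to return to the original schedule.
- **The day 40 and day 180 example costs the primary endpoint.** It does not. The second delay falls after the day 127 sample.
- **One adverse-event hold leads to discontinuation under Section 5.5.1.** That section says "One vaccine and/or one CDX-1127 delay up to 21 days is allowed if due to an AE, regardless of attribution" and stops the causative drug after more than one delay of 7 days or more. A hold of 9 days or more at vaccine 2 would put vaccine 3 at least 9 − 2 = 7 days late by the same arithmetic. However, counting from the original date is stated only for Table 7, and Section 5.5.1 allows doses to be shifted. Whether the shifted vaccine is a second delay is unclear, not settled.
- **The loss will differ by arm because adverse events do.** Footnote a belongs to the table for delays not due to toxicity, so this does not follow.

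**Conclusion.** The plan is wrong as written, on two counts that need no assumption about delay rates. First, two deviation-free vaccinations (days 36 and 176) can meet footnote a. Second, a vaccine 2 delay of 5 to 7 days, which Table 7 treats but records as a deviation, meets footnote a by itself through the spacing rule.

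The effect on the primary endpoint is narrower than the contradiction. On the current schedule, removal before day 127 needs at least one recorded deviation among vaccines 1 to 3, either with a late vaccine 4 or through the knock-on. The figures of 3%, 10% and 22% show scale under assumed, independent delay rates. They are neither a forecast nor a bound. A reader might add the booster and quote higher removal rates, but those would not measure loss of persistent response. At the middle assumption the loss is about the whole allowance of 4, which also has to cover ineligibility and other dropout.

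The footnote does not say whether protocol treatment means the vaccine alone or also CDX-1127 in Arm A. Section 5.6 uses the term broadly, which suggests both, but the text leaves it open.

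**What to change.** The sponsor should reconcile footnote a with the Table 7 windows, the 5-day minimum spacing and Section 5.6, so that one consistent rule decides whether a participant with delayed vaccinations stays on treatment. The text should state whether footnote a stops the vaccine only or CDX-1127 as well. Section 5.5.1 should say whether a later vaccine moved because of a single adverse-event hold counts as a second delay. The limits, and which of the conflicting rules prevails, are for the clinical team.

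The cost is a wording amendment, with no extra visits, drug or participants.

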## 5.6 Discontinuation of Therapy

Protocol treatment will be discontinued for any of the following reasons:

- Any dose-limiting toxicity as defined in [Section 8.9](#).
- Disease progression requiring other therapy (e.g. surgery under general anesthesia, radiation, chemotherapy, or steroid therapy). The appearance of small metastases or recurrent tumor deposits will not be a basis for discontinuing the study treatment. Biopsy to determine the nature of new lesions or minor surgical procedures to excise a new lesion (with or without anesthesia) will not be a basis for discontinuing study treatment.
- Initiation of cytotoxic chemotherapy, radiation therapy, surgery for resection of disease, steroid therapy, or other immunosuppressive therapy.
- Any other potential adverse reaction deemed sufficiently serious to warrant discontinuation of therapy by the Principal Investigator or one of the Associate Investigators.

- Noncompliance with the requirements of the study.
- Therapy may be discontinued at the participant's request.
- Therapy may be discontinued at the discretion of an Investigator.
- Pregnancy. Pregnant participants will continue to be followed for the duration of the pregnancy.

Participants who discontinue treatment will be followed according to the follow-up schedule outlined in [Section 9.1](#), unless a participant has withdrawn consent.

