### **5.7 Replacement of Study Participants**

A participant who is enrolled but does not receive study drug or does not undergo any of the study related procedures may be replaced. Every attempt will be made to evaluate any data from these participants for endpoint assessment.

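### Minor: one vaccine 2 visit that is 5 to 7 days late for a non-toxicity reason takes the participant off treatment, because the 5-day minimum gap makes vaccine 3 count as a second delay

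*Combined protocol and SAP*

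**What the plan says.** Section 5.5.2 and Table 7 govern visits delayed for reasons other than toxicity. Five rules bear on a late vaccine 2:

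- **Counting.** "The range of days is counted from the original scheduled date". A late dose therefore does not reset the clock for the next one.
- **Spacing.** Participants should go back to the original schedule as soon as they can, subject to "a minimum of 5 days in between vaccines".
- **What is given.** Section 5.5.2 says Table 7 settles "whether the participant should continue to be treated". Its day 8 and day 15 rows both give the vaccine at 3 to 7 days off schedule and record a deviation. At 8 or more days, the day 8 row gives nothing.
- **Catch-up.** The text before the table says "the missed treatment will be administered as soon as possible, so that subsequent treatments will be given in the appropriate intervals".
- **Removal.** Footnote a, attached to the column of day ranges: "A participant will be taken off protocol treatment if more than one vaccination is delayed [3 days or more] during the treatment period". It has no exception for a delay forced by the spacing rule.

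Section 5.6 sets what follows removal: "Participants who discontinue treatment will be followed according to the follow-up schedule outlined in" section 9.1. The end-of-treatment calendar there draws research blood only at EOT 1 and EOT 2. Section 7.1.2 counts a participant as evaluable for the primary immune endpoint in three cases: a baseline and a day-127 assessment, progression before day 127, or a stop for dose-limiting toxicity. Under section 5.7, a participant who "does not receive study drug or does not undergo any of the study related procedures may be replaced"; this does not clearly reach someone already dosed and sampled.

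**The concern.** Each rule is reasonable alone. Together they let one late visit use up the whole tolerance of footnote a, which is meant to act on more than one delayed vaccination. A site that follows every instruction (give vaccine 2 on day 13 to 15, respect the gap, give vaccine 3 as early as allowed) must then take the participant off treatment.

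The result is also out of order. Under the Table 7 row, a participant who returns one to four days later than that, on day 16 or 17, skips vaccine 2, has vaccine 3 inside its ordinary window and continues.

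At stake is a place in the primary immune analysis. Removal for delay is not one of the evaluable categories in section 7.1.2, and no day-127 blood is scheduled after removal.

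**Working it through.** **Inputs.** Vaccine days 1, 8, 15 and 36 (section 5.2.1, current schedule). Minimum gap 5 days, delay counted from the original date (section 5.5.2). Removal when more than one vaccination is 3 or more days late (footnote a). The plan states no figure to reproduce here; the check is calendar arithmetic.

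**Formula.** If vaccine 2 is *d* days late, it is given on day 8 + *d*. The earliest vaccine 3 is day max(15, 8 + *d* + 5), so from *d* = 2 upward vaccine 3 is *d* − 2 days late. That reaches 3 when *d* is 5 or more.

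| Vaccine 2 late by | Vaccine 2 day | Earliest vaccine 3 | Vaccine 3 late by | Delays of 3+ days | Footnote a |
|---|---|---|---|---|---|
| 3 | 11 | 16 | 1 | 1 | stays |
| 4 | 12 | 17 | 2 | 1 | stays |
| 5 | 13 | 18 | 3 | 2 | off |
| 6 | 14 | 19 | 4 | 2 | off |
| 7 | 15 | 20 | 5 | 2 | off |

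Of the 5 late days on which Table 7 gives vaccine 2 as a deviation, 3 lead to removal. If the gap means 5 full days between doses (a date difference of 6), vaccine 3 is *d* − 1 days late and 4 of the 5 lead to removal.

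**Return on day 16 or 17.** Vaccine 2 is 8 or 9 days late, so Table 7 gives none. Vaccine 3 on that day is 1 or 2 days late, inside its ±2-day window. Even if the skipped dose counts as delayed, there is only one delay, and the participant stays on.

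**Vaccine 4.** Day 36 is 36 − 20 = 16 to 36 − 18 = 18 days after vaccine 3, so it is not forced late. The knock-on ends at vaccine 3.

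**What removal costs.** The calendar has 10 research draws (days 1, 15, 22, 36, 57, 78, 85, 127, 176, 183). The 8 from day 22 onward give way to EOT 1 and EOT 2. If EOT 1 falls on day 18 to 20 (an assumption), EOT 2 falls 7 days later, on day 25 to 27, which is 127 − 27 = 100 to 127 − 25 = 102 days before day 127. The participant also loses vaccine 4, the day-176 booster and, in Arm A, 2 of 3 CDX-1127 infusions (days 36 and 78). Against a target of 15 evaluable per arm, one loss is 1/15 = 6.7%. The accrual ceiling leaves 34 − 30 = 4 places for losses from all causes.

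**Biopsy.** The day-22 biopsy is meant to fall one week after vaccine 3. With vaccine 3 on day 18 to 20, day 22 is only 22 − 20 = 2 to 22 − 18 = 4 days after it. Keeping the week moves the biopsy to day 25 to 27, which is 3 to 5 days late. The day 22 row of Table 7 allows that as a recorded deviation.

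**The case against.** **Footnote a is a cap, not a contradiction.** It sits on the column heading and so qualifies every row. The rows say what to give at a visit; the footnote limits how many late doses are tolerated. The day 15 row still serves anyone whose first delay is vaccine 3. Removing a participant with two of three weekly priming doses off schedule is strict but coherent. This stands as a defence of having a cap. It does not explain why someone who returns later stays on.

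**A shifted-series reading exists.** The catch-up sentence speaks of suitable intervals for later doses, and the next sentence lets treatment run longer if needed. On that reading, a correctly spaced vaccine 3 is not a delay of its own. This has some support, so a reader who infers that removal follows under every reading goes too far. But counting from the original date points the other way, and nothing in section 5.5.2 waives footnote a.

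**The loss may be absorbed.** Up to 34 may be accrued for 30 evaluable, about 17 per arm, so early removals come first out of that allowance. A removed participant with two evaluable draws, including baseline, stays in the other immune analyses. Both points stand.

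**Retention disturbs the week-3 biopsy.** This is true, and under the current schedule it is the only vaccine-site biopsy. But the end-of-treatment calendar schedules no biopsy, so removal before day 22 does not protect that sample either.

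**Two stronger readings are tempting.**

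- A reader might infer that section 5.5.1 would keep a participant with the same dates after an adverse event, since its discontinuation condition is "If there is more than one vaccine and/or one CDX-1127 delay by 7 days or more due to an AE". The same section also allows one delay of up to 21 days, and this case has two delays, so the outcome is not clear. A different threshold for adverse events is not in itself a fault.
- A reader might infer that the section 7.2 criterion for further study is in danger. With no frequency given, and with allowance places to absorb losses, the documents do not support that. Section 7.5 also describes the study as one of estimation.

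**Conclusion.** The point holds as a minor operational inconsistency. Under section 5.5.2 as written, a non-toxicity delay of vaccine 2 by 5 to 7 days, which Table 7 still treats, makes vaccine 3 at least 3 days late. Footnote a then ends treatment for one late visit. Without progression before day 127, the participant leaves the evaluable set for persistent response.

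This rests on three assumptions: delay is counted from the original date for footnote a as well as for the rows, the gap is a 5-day date difference (a stricter reading widens the range to 4 to 7 days), and no day-127 blood is drawn outside the calendar. The contrast with a day 16 or 17 return also assumes that the Table 7 row governs rather than the catch-up sentence; that is the better reading, since section 5.5.2 gives Table 7 that task. How often such a delay occurs is unknown and may be zero.

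**What to change.** Add one clause to footnote a: *not counting a vaccination delayed only to keep the 5-day minimum gap after a late prior vaccination*. A vaccine 2 that is 5 to 7 days late, followed by vaccine 3 on the earliest permitted day, then counts as one delay and the participant continues. If vaccine 3 is given later than the gap requires, it is not late only because of the gap, so it still counts. The 3-day threshold, the gap and the Table 7 windows stay as they are.

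The cost is a wording change, with no added visit, procedure or draw. The one downside should be accepted openly. For these participants the biopsy is either done on day 22, only 2 to 4 days after vaccine 3, or moved to about day 25 to 27 as a recorded deviation to keep the one-week interval. The site instructions should say which.

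The documents do not say whether dosing is complete. If it is, the useful step is to report how footnote a was applied and whether anyone was removed under it.
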